#### Single-session videoconference-delivered skills-based pain class (Empowered Relief)

Our group developed the single-session intervention (SSI) for pain management in 2013 with the goal of rapidly equipping patients with skills to self-regulate pain-specific distress. Pilot data revealed significantly reduced pain-specific distress—as indexed by reductions in pain catastrophizing—1 month post-treatment, regardless of comorbid depression and anxiety [25]. The SSI (Empowered Relief) was also the subject of a NIH-funded randomized controlled trial in chronic low back pain [29]; the findings showed that Empowered Relief was non-inferior to an 8-week cognitive behavioral therapy and superior to a health education class for reducing pain catastrophizing and improving multiple secondary outcomes at 3 months post-treatment.

For the present study, for the first time, we seek to pilot test the impact of “Empowered Relief,” a group-based SSI that is delivered online, on bolstering pain and symptom management in adults with mixed etiology chronic pain. A clinical psychologist trained in delivering the 2-h intervention will administer the class via the Zoom platform to groups of enrolled participants. The class is delivered by PowerPoint presentation and includes mind-body pain science, the importance of self-regulation in the context of pain and stress, and evidence-based skills that target pain-specific distress and enhance pain control. Participants will be guided in developing their own self-treatment plan and acquiring the skills necessary to decrease pain and stress-related physiological hyperarousal and to enhance regulation of cognition and emotion within the context of pain. At the end of the class, participants will (1) develop a self-tailored personalized plan to target pain-specific distress, (2) receive a 20-min guided relaxation response audio file, and (3) obtain an electronic copy of the didactic class content. Cohort effects are expected to be minimal due to the single session nature of the class, the highly structured and manualized nature of the class, and the minimal participant interaction via a videoconference platform.

#### Usual care (waitlist control) arm

The control condition will be a usual care comparator, which was selected because clinical trial methodologists [36, 37] argue that waitlist or usual care controls are appropriate for early-phase, proof-of-principle trials where the goal is to promote innovation. Participants in the usual care group will not receive a study intervention and will be instructed by a research study coordinator to continue with the care they would normally receive as part of their ongoing clinical care. Upon completion of all study measures, participants in the usual care condition will be given the opportunity to participate in the intervention arm so as to ensure equality in study participation.

### Class platform

All treatment sessions will occur via the Zoom platform that is password-protected and hosted within the fire-walled Stanford University School of Medicine and Stanford HealthCare systems.

### Instructors

For the ER treatment group, all instructors will be doctoral-level clinical psychologists trained in the treatment of chronic pain.

### Training and monitoring of instructors

ER instructors will be trained in the study protocol for their classes prior to administering treatment. Existing treatment manuals as well as highly structured and standardized class content will assure treatment fidelity. A research coordinator, serving as a fidelity rater, will directly observe the ER classes. Cohort effects are likely to be minimal due to the single-session format and relatively minimal participant interaction.

### Measures

Demographic data, pain characteristics, and physical and psychosocial health measures will be collected at enrollment. Pain catastrophizing will be assessed using the Pain Catastrophizing Scale [38]. Pain bothersomeness will be assessed by a single-item question that is commonly used in chronic low back pain research [39, 40]. PROMIS measures will be used to assess sleep disturbance, pain intensity, pain interference, physical function, depression, and anxiety using short forms [41]. Our group has applied the NIH PROMIS measures in multiple nationally funded clinical pain treatment trials and other studies [42–44] (Table 3).

**Table 3 Tab3:** Baseline and follow-up measures

Measurement	Brief measure description	Baseline Pre-class survey	Follow-up week 1 (ER class only)	Post-treatment Week 2	Post-treatment Months 1, 2, and 3
Demographics	Date of birth, gender, ethnicity, race, education level, household income, employment, and marital status.	x			
Pain Catastrophizing Scale (PCS) [31]	13-item scale assesses the severity of trait pain catastrophizing tendencies on a 5-point scale (0 = “not at all”; 4 = “all the time”); sum scores range from 0 to 52. The PCS has 3 factors (helplessness, magnification, rumination) and has good psychometrics [31]. Higher score reflects more catastrophizing.	x		x	x
PROMIS measures [27]	NIH PROMIS measures will be used to assess multiple variables of interest, including pain intensity, pain interference, physical function, depression, anxiety, sleep disturbance, social isolation, anger, and fatigue. Short form 4- to 8-item measures will be used to minimize participant burden.	x		x	x
Pain bothersomeness	Single-item measure of pain bothersomeness in the past week from “not at all bothersome” to “extremely bothersome.”	x		x	x
COVID-19	4-item if tested negative and 9-item if tested positive for COVID-19. Assess how the coronavirus impacts chronic pain, day-to-day life, depression, and psychological health.	x			x
Satisfaction with treatment and Zoom (ER group only)	ER group will answer a 13-item survey that assesses the class experience and using Zoom (video-conferencing) as it relates to engagement, relevancy, and usefulness.		x		
Skill use (ER group only)	ER group will answer 5 questions assessing the frequency of skills use learned in class over the past week, from “not at all” to “several times a day.”		x		

#### Baseline (pre-treatment) assessment

Three to 6 days pre-treatment, patients will complete an online baseline survey including demographic information, pain condition and characteristics, pain bothersomeness, pain catastrophizing, and the PROMIS measures. Participants will not be asked to repeat demographic information again, but these measures will be identical to those assessed post-treatment.

#### Post-treatment assessment

One week post-treatment, patients in the ER arm will complete a brief questionnaire assessing patient satisfaction with the intervention, in addition to their frequency of skills use and audio file use. At 2 weeks and 1, 2, and 3 months post-treatment, all participants will complete a set of questionnaires identical to those administered at baseline. The primary study endpoint is 1 month post-treatment. Participants may receive up to $50 for study completion.

##### Primary outcome measure

Our primary outcome measure is pain-specific distress as indexed by pain catastrophizing scores at 1 month post-treatment. Pain catastrophizing will be assessed using the Pain Catastrophizing Scale (PCS), and a total score will be generated using the sum of the 13-items of the PCS. The PCS has valid and reliable psychometrics [38].

##### Secondary outcome measures

Our secondary outcome is pain bothersomeness, whereby participants rate their chronic pain bothersomeness during the previous 7 days on a 0 to 10 numeric rating scale anchored by 0 (not at all bothersome) and 10 (extremely bothersome) that is commonly used in CLBP research [39, 40]. PROMIS sleep disturbance will be assessed with the NIH PROMIS sleep disturbance short form.

##### Tertiary outcome measures

NIH PROMIS measures [41] will be administered to assess pain intensity, anxiety, depression, and physical function. These measures have been successfully applied to pain research [45–48].

### Data collection, quality control, and confidentiality

The online assessments completed by participants will be gathered securely in a REDCap database. No questionnaires will be collected on paper. Additionally, the members of the team will be trained to use and complete case report forms (CRFs), how to review them for completeness, and how to maintain participant confidentiality. The patient flow will be reported according to the Consolidated Standards of Reporting Trials (CONSORT) guidelines [49].

### Protection of human participants and assessment of safety

#### Protection of human participants

The Stanford University Institutional Review Board (IRB) has approved this study.

#### Safety monitoring

This trial will not be monitored by an independent Data and Safety Monitoring Board (DSMB). However, two researchers composed of a physician and a clinical psychologist with knowledge in the treatment of chronic pain conditions will oversee the project. In addition, we have a dedicated research regulatory manager who will provide oversight for all regulatory processes. The team will meet twice a year or on an as-needed basis and will make relevant safety decisions regarding reported participant cases.

#### Adverse experiences

The treatments in this study are not anticipated to pose any risks to participants. However, a study coordinator will review enrolled patient records periodically to monitor for adverse events. In the case of an adverse event, an adverse event case report form will be completed. These will be discussed in monthly team meetings and reported to the IRB annually. Serious adverse events will be reported to the Stanford IRB and NIH. The PI and study committee will evaluate all serious adverse events within 24 h after the study team becomes aware of the incident. All study-related adverse events will be included in the annual report to the NIH, and serious adverse events will be reported within 2 weeks.

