### Study sample and setting

Participants for this trial will be recruited through targeted emails and advertisements at Stanford’s pain management clinics, in addition to the Stanford Systems Neuroscience and Pain Lab (SNAPL) database. All advertisements will direct interested individuals to an online screening form that assesses for initial eligibility. The study will enroll 120 adults (age >18 years) with a chronic non-cancer pain condition and who meet the study criteria (Table 1). The sample size accounts for expected attrition, and eligibility will be assessed by the research staff.

**Table 1 Tab1:** Inclusion criteria

Inclusion criteria	Rationale	Sources
Pain ≥3 months more than half the time	Study restricted to non-cancer chronic pain	A, TS
English fluency	Ability to complete study procedures	A, TS
Ability to adhere to and complete study protocols		A, TS
Males and females, 18+	Not including children	A, TS

*A*, automated data gathered from REDCap surveys; *TS*, telephone screening

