#### Stopping rules

The trial will be stopped if (1) either treatment intervention is associated with adverse effects that calls into question the safety of the intervention, (2) there is difficulty in study recruitment or retention that will impact the ability to evaluate study endpoints, (3) new information becomes available during the trial that indicates the need to stop the trial, or (4) other unforeseen situations occur that would warrant stopping the study.

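### Record review is the only active search for adverse events described in a fully online trial; the existing surveys should also ask both arms about them

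*Protocol article*

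**What the plan says.** Under Adverse experiences, the protocol article expects no harm ("The treatments in this study are not anticipated to pose any risks to participants") but still commits to monitoring: "a study coordinator will review enrolled patient records periodically to monitor for adverse events". It does not say which records are meant or how often they are read. What follows detection is set out: "In the case of an adverse event, an adverse event case report form will be completed", then discussion at team meetings and reports to the IRB and NIH.

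Under Safety monitoring there is no independent board. The study's own team "will make relevant safety decisions regarding reported participant cases". The first ground under Stopping rules is that "either treatment intervention is associated with adverse effects that calls into question the safety of the intervention".

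Three other sections bear on whether events would be found:

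- Study sample and setting: recruitment is through the institution's pain clinics, "in addition to the Stanford Systems Neuroscience and Pain Lab (SNAPL) database".
- Class platform, and Data collection, quality control, and confidentiality: the class runs by videoconference, and "The online assessments completed by participants will be gathered securely in a REDCap database". No paper forms are used.
- Measures, Table 3, and Post-treatment assessment: both arms complete surveys at week 2 and months 1, 2 and 3. The table lists the survey content in some detail, including a COVID-19 module and a 13-item satisfaction survey for the class arm, but no adverse-event item.

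**The concern.** The article does not leave detection of adverse events to another document. It names a method, and that method fits the setting poorly. Participants have no in-person study visit at which an event might come up, and neither eligibility table requires current care at the site. Events plausible after a psychological class, such as a spell of heightened distress or a pain flare, need not lead to a clinic contact.

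At stake is what a low or zero count of adverse events would mean. With the plan followed exactly, a report of none could mean that none occurred, or that none reached a record and none was volunteered. The team's safety decisions, the first stopping rule and the IRB and NIH reports all draw on the same input.

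**Working it through.** **1. Is there a safety figure to reproduce?** No. The article gives no expected event rate, no numerical safety threshold and no power for safety. The only usable number is the arm size: 120 enrolled, randomized 1:1, gives 120 / 2 = 60 per arm.

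**2. What could the described method see?** The word records is not defined, so take both readings.

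- *Medical charts.* The review sees what a clinician wrote down. The trial itself generates no chart entries, because class and assessments are online. Whether those recruited from the research database have a current chart at the site is not stated.
- *Study records.* These consist largely of the REDCap surveys, and Table 3 shows no adverse-event question in them.

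Some events can be missed on either reading.

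**3. Do the outcome scores fill the gap?** Table 3 asks both arms about pain intensity, pain bothersomeness, catastrophizing, anxiety, depression, sleep, fatigue and anger at every follow-up from week 2. Worsening in these areas is therefore measured, and equally in both arms. But no section says that a score is screened for safety or triggers an adverse event form. Under Primary analyses and Secondary objectives the outcomes are compared as arm means and as proportions improving by at least 30%. Neither summary shows that an individual got worse.

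**4. Do volunteered reports fill it?** They are possible, since the team acts on reported cases. But the arms have unequal occasions to volunteer. The class arm attends a session observed by a research coordinator and completes an extra week-1 survey; the waitlist arm has neither.

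**5. Illustration of size.** Let p be the true proportion with an event and s the share of events that reach a record. Both are assumed, because the article gives neither. With n = 60 in the class arm:

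P(at least one recorded) = 1 − (1 − p·s)^60, and expected number recorded = 60·p·s.

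For p = 0.05:

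- s = 1: 1 − 0.95^60 = 0.954, with 3.0 events expected
- s = 0.75: 1 − 0.9625^60 = 0.899, with 2.25 expected
- s = 0.50: 1 − 0.975^60 = 0.781, with 1.5 expected
- s = 0.25: 1 − 0.9875^60 = 0.530, with 0.75 expected

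Over a range of true rates, the chance of recording at least one event is:

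| True rate p | s = 1 | s = 0.75 | s = 0.50 | s = 0.25 |
|---|---|---|---|---|
| 2% | 70% | 60% | 45% | 26% |
| 5% | 95% | 90% | 78% | 53% |
| 10% | 99.8% | 99% | 95% | 78% |

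Capture matters most when events are uncommon, which is what the article expects here. The table does not estimate the loss in this trial.

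**The case against.** The strongest reply is that this is a condensed article about a two-hour education class. How events are elicited, from which records and how often could well be in the full protocol or the IRB submission. Nothing under Adverse experiences is false or contradicts another section. The surveys already ask both arms about the very problems one would worry about, and cases can reach the team by report. The first stopping rule is qualitative and is not triggered by a single event, so the probabilities above do not show that it fails.

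Much of this stands, and it rules out several stronger readings that a reader might infer:

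- *That a safety comparison between arms is compromised.* None is planned. The hypotheses and analyses cover efficacy outcomes only.
- *That record review is the sole route, or that participants are never asked about harm.* Reported cases are allowed for, and the surveys measure pain and distress directly.
- *That database recruits have no chart, or that records means charts.* The article says neither.
- *That capture is known to differ by arm.* Recruitment source and prior clinic use are fixed before randomization and balanced in expectation. The unequal occasions to volunteer a report are a possibility, not a demonstrated imbalance.

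The reply does not remove the point itself. The article states a method instead of deferring it, the weakness appears under either meaning of records, and no text carries a worsening score to the adverse event form.

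**Conclusion.** The concern holds in a limited form. The one active search described can miss events that reach no record and are not volunteered. That weakens the trial's safety reporting and the information available to the first stopping rule. No estimate, power figure or efficacy conclusion is affected.

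The amount of under-capture cannot be derived from the article; the percentages above rest on assumed event rates and assumed capture shares. The conclusion also assumes that no fuller document already provides for direct questioning. Given a low-risk class, this is a minor point, worth acting on because the remedy is cheap.

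**What to change.** Add one or two adverse-event items to the existing REDCap surveys at week 2 and months 1, 2 and 3, worded identically in both arms. An example is a question about any new or worsened physical or emotional problem since the last survey, with free text. Keep record review as a second source, since survey items miss those who do not respond. Under Adverse experiences, name the records, give the review interval, and state that both sources feed the adverse event form and the safety review. If the full protocol already does this, align the article with it.

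The cost is a survey edit, a minor IRB amendment, roughly a minute per participant per survey, and some additional non-serious reports to review. No new visits are needed, and no efficacy outcome, sample size or clinical rule changes.

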#### Stopping rules

The trial will be stopped if (1) either treatment intervention is associated with adverse effects that calls into question the safety of the intervention, (2) there is difficulty in study recruitment or retention that will impact the ability to evaluate study endpoints, (3) new information becomes available during the trial that indicates the need to stop the trial, or (4) other unforeseen situations occur that would warrant stopping the study.

### Statistical issues

#### Sample size and detectable differences

We chose our sample size to ensure adequate power to detect treatment effects on the primary outcome (i.e., pain catastrophizing). The project will enroll 120 participants (ages >18 years) with a diagnosis of chronic non-cancer pain (>3 months more than half the time).

To compare the main effect of ER class on pain catastrophizing scores against the WLC condition, we will plan to enroll 120 participants and have 116 completers (58 per group). The proposed sample size accounts for 4% attrition in each study arm. This is lower than the attrition rate we observed in our Empowered Relief trial [29] of 14.9% or of that seen in pain CBT literature of 18–25% [50, 51], but we believe that the digital format and single-session nature of the intervention will be less burdensome and lead to lower attrition rates. We hope to achieve 80% power to detect medium-large treatment effects on the primary outcome (i.e., pain catastrophizing).

### Statistical analyses

#### Primary analyses

We will use an intent-to-treat approach in all analyses (i.e., the assessment of individuals will be analyzed by a randomized group regardless of participation in the intervention). By doing so, we protect against any confounds that arise as a result of subject dropout.

The main effect of ER on pain catastrophizing will be compared against the WLC using a 2-sample *t* test. Our primary endpoint is pain catastrophizing at 1 month post-treatment. We will also compare the proportion of success rate, defined as ≥30% reduction in pain catastrophizing for a clinically significant treatment response [52].

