## Specific aims

Our specific aim and three corresponding hypotheses are outlined below.
We will conduct a randomized controlled trial comparing the preliminary effects of a single-session videoconference-delivered pain education class compared to a waitlist control (i.e., usual care) condition.
Hypothesis 1: The single-session intervention (Empowered Relief (ER)) will lead to greater reductions in pain catastrophizing compared to a usual care condition.Hypothesis 2: ER will lead to greater reductions in pain bothersomeness and sleep disturbance compared to a usual care condition.Hypothesis 3: ER will lead to greater reductions in pain intensity, anxiety, depression, and physical function compared to a usual care condition.

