### Recruitment procedures

Because the study intervention is group-based and delivered via videoconference, we are recruiting participants in 2–3 large cohorts consisting of 30 participants per class cohort (minimum of 20 participants, maximum of 30 participants per cohort) for both study arms.

Interested individuals deemed initially eligible by the online screening will be further screened over the phone. Eligible individuals will then be invited to enroll in the study and consented with a research staff over the phone, after which they provide an electronic signature to the consent form emailed to them. Participants are randomized following eligibility confirmation and informed consent procedures. Then, participants complete the enrollment survey, which includes information related to their chronic pain and psychosocial well-being.

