### Blinding

Participants cannot and will not be blinded to the study arm they are randomized to. A clinical psychologist who will be trained in the intervention and has no involvement in the data analysis will deliver the intervention. The study coordinator will be responsible for handling the randomization process through REDCap but will remain blinded to the randomization scheme. All data given to the statistician will be blinded. All research data will be kept separate from identifiers and linked using a participant number. Only the principal investigator will have access to the file linking names and participant numbers, and the file will be stored behind password-protected and fire-walled systems. The team will have access to the final unidentified dataset.

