#### Secondary objectives

To test the secondary and tertiary aims that the ER class will have greater reductions in pain bothersomeness, sleep disruption, pain intensity, anxiety, depression, and physical function compared to WLC, our primary endpoint will be considered at 1 month post-treatment, and its within-subject difference from baseline will be calculated. The mean difference in the ER group will be compared against the WLC arm using the two-sample *t* test. Similarly, we will also compare the proportion of success rate, defined as ≥30% reduction in our outcomes for a clinically significant treatment response [52].

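### The primary t test on 1-month PCS is valid but ignores baseline PCS; ANCOVA would be more precise, provided baseline is recorded before allocation is known

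*Protocol article*

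**What the plan says.** Under Primary analyses, the protocol article states: "The main effect of ER on pain catastrophizing will be compared against the WLC using a 2-sample" t test. It adds: "Our primary endpoint is pain catastrophizing at 1 month post-treatment". The Primary outcome measure section agrees, defining the outcome as "pain-specific distress as indexed by pain catastrophizing scores at 1 month post-treatment". No covariate is named in either place.

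Hypothesis 1, under Specific aims, is worded as a reduction: the class "will lead to greater reductions in pain catastrophizing compared to a usual care condition". Under Secondary objectives, the other outcomes are taken at 1 month and "its within-subject difference from baseline will be calculated"; the mean changes are then compared by two-sample t test.

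Baseline PCS will be available: "Three to 6 days pre-treatment, patients will complete an online baseline survey including demographic information, pain condition and characteristics, pain bothersomeness, pain catastrophizing", followed by the PROMIS measures. On its timing, Recruitment procedures says: "Participants are randomized following eligibility confirmation and informed consent procedures. Then, participants complete the enrollment survey". The Blinding section says: "Participants cannot and will not be blinded to the study arm they are randomized to".

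**The concern.** A patient's PCS at baseline is likely to be a good predictor of the same patient's PCS a month later. A t test on the 1-month score leaves that predictable variation in the error term. A t test on change removes it by subtracting the whole baseline value. That subtracts too much unless the correlation is close to 1, and below a correlation of 0.5 it is noisier than ignoring baseline altogether. ANCOVA estimates how much to subtract.

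What is at stake is precision. The protocol hopes for 80% power and allows 4% attrition, while citing 14.9% in the team's earlier trial of the same class. A primary analysis with a smaller residual variance would give that plan some slack without another patient or questionnaire.

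**Working it through.** **Inputs.** From Sample size and detectable differences: 120 enrolled, 116 completers, 58 per arm, 80% power, and an effect described only as medium to large. Not given, and therefore assumed: two-sided alpha 0.05, the standardised effect d (in SDs of 1-month PCS), the correlation rho between baseline and 1-month PCS, and equal SDs at the two times.

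**The plan's own figure.** It cannot be reproduced exactly without alpha, an SD and a numeric effect, so I solved backwards. For a two-sample t test the noncentrality is d × √(n/2). With n = 58, √29 = 5.385, and d = 0.525 gives 2.827 on 114 degrees of freedom, which is 80% power. That effect fits the protocol's description. At d = 0.5 the power is 76%, and at d = 0.6 it is 89%.

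**Variance relative to the t test on 1-month scores.**
- 1-month score: 1
- Change score: 2(1 − rho)
- ANCOVA: 1 − rho²

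Change minus ANCOVA is 2(1 − rho) − (1 − rho²) = (1 − rho)². The 1-month score minus ANCOVA is rho². Neither difference can be negative, so ANCOVA is never worse than either, apart from one degree of freedom and a small allowance for chance baseline imbalance.

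**Power at 58 per arm, d = 0.525.** Each noncentrality is 2.827 divided by the square root of the variance factor.

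| rho | Change: factor | Change: power | ANCOVA: factor | ANCOVA: power | 1-month score: power |
|---|---|---|---|---|---|
| 0.3 | 1.40 | 66% | 0.91 | 84% | 80% |
| 0.5 | 1.00 | 80% | 0.75 | 90% | 80% |
| 0.6 | 0.80 | 88% | 0.64 | 94% | 80% |
| 0.7 | 0.60 | 95% | 0.51 | 98% | 80% |

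Multiplying the ANCOVA variance by 1 + 1/(2n − 4) = 1 + 1/112, to allow for chance baseline imbalance, gives 83, 90, 94 and 97%. If rho were 0, ANCOVA would have 79.6%, so the worst loss is about 0.4 points. Simulation (20,000 replicates, 58 per arm) agreed at rho 0, 0.5, 0.6 and 0.7.

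**More attrition.** 120 × (1 − 0.149) = 102, or 51 per arm. At d = 0.525 the 1-month t test then has 75% power, and ANCOVA at rho 0.5 has 85%.

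**Baseline recorded after allocation is known.** Suppose that learning the allocation shifts reported baseline PCS in one arm by s SDs, with no lasting effect and no true treatment effect. The expected bias is 0 for the 1-month score, rho × s for ANCOVA and s for change. With s assumed between 0.1 and 0.3, simulation gave:

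| Analysis | Bias, rho 0.5 (SD) | Type I error, rho 0.5 | Bias, rho 0.7 (SD) | Type I error, rho 0.7 |
|---|---|---|---|---|
| 1-month score | 0 | 5% | 0 | 5% |
| ANCOVA | 0.05 to 0.15 | 6 to 15% | 0.07 to 0.21 | 8 to 34% |
| Change | 0.1 to 0.3 | 8 to 36% | 0.1 to 0.3 | 11 to 54% |

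**The case against.** The strongest objection is that adjustment is not free in this trial. Baseline PCS is self-reported after randomisation by participants who are not blinded, and the protocol does not say when they learn their arm. If that knowledge alters what they report, ANCOVA carries part of the shift into the estimate, while the planned 1-month comparison does not. A complete-case ANCOVA would also drop anyone randomised without a baseline survey, against the intent-to-treat commitment. This stands, and it sets conditions on the remedy. It does not favour the plan as a whole: the change scores for the other outcomes carry the full shift, and the 30% responder comparison, including the one for PCS, uses the same baseline.

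A second objection is that the gain depends on rho, which the documents do not give. At rho 0.3 it is only 3 to 4 points over the 1-month t test, and at rho 0.7 the change score is already close to ANCOVA. That is also true, but the direction of the gain does not depend on rho.

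Three stronger readings might be inferred, and the documents do not support them.
- *The primary test is wrong.* In a randomised comparison it is unbiased with the correct type I error. Its standard error already allows for chance baseline imbalance, so what is lost is precision.
- *The trial is underpowered as planned.* 58 per arm gives 80% power at d of about 0.525, which is compatible with the protocol's description.
- *The primary test fails to address reductions, or targets a different quantity from the other tests.* If allocation does not affect baseline, the 1-month difference, the difference in change and the ANCOVA coefficient share one expected value for a given outcome. Only their variances differ.

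**Conclusion.** This is a cheap improvement and not an error. The primary comparison is valid but inefficient, and the change-score tests planned for the other outcomes are never more efficient than ANCOVA beyond a trivial loss of degrees of freedom. At 58 per arm and d = 0.525, ANCOVA raises power from 80% to about 84, 90, 94 and 98% at rho 0.3, 0.5, 0.6 and 0.7. These sizes rest on assumed values of alpha, d and rho and on equal SDs. The recommendation also depends on baseline being recorded before participants know their arm; without that, adjustment exchanges some precision for a possible bias.

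The protocol never says outright whether the primary t test uses the 1-month score or the change. The literal reading is the 1-month score. The efficiency argument holds under either reading, and naming the model settles the matter.

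**What to change.** 1. Make the primary analysis an ANCOVA of 1-month PCS on arm and baseline PCS, reporting the adjusted mean difference with its 95% confidence interval as the answer to Hypothesis 1.
2. Use the same model, with its own baseline, for each secondary and tertiary outcome in place of the change-score t tests.
3. Keep the unadjusted 1-month comparison as a sensitivity analysis.
4. Require the baseline survey to be completed before allocation is generated or, at the least, before it is disclosed.
5. Keep participants with a missing baseline value in the analysis, for example by imputing the overall baseline mean.

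The cost is a change in survey order and slightly more analysis work; no extra patients or measures are needed. For any participants whose baseline was recorded after disclosure, a reporting shift could enter the adjusted estimate, and the unadjusted comparison in step 3 should then be read beside it.
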